#### Protocol deviations

Any deviations from the protocol will be fully documented on a protocol deviation form that will be sent to the sponsor and stored in the trial master file and on site in the study site file.

### Plans to give access to the full protocol, participant-level data and statistical code {31c}

There are currently no plans to grant public access to the full protocol, participant-level dataset or the statistical code.

## Oversight and monitoring

### Composition of the coordinating centre and trial steering committee {5d}

IPM will jointly coordinate the trial with the sponsor, the University of Oxford.

As well as a central trial coordination team to coordinate the day-to-day activities of the trial, IPM will deploy one clinical research associate and two clinical study nurses to each district who will assist the sites with the recruitment, data collection and conduct monitoring activities. IPM will also be primarily responsible for data management but supported by the University of Oxford.

The University of Oxford will coordinate the sponsor activities, coordinate the trial committees and provide day-to-day management and oversight of the trial.

The TOC is coordinated by the University of Oxford and is composed of members from each of the study partners to review the operational management of the trial and discuss any urgent matters related to trial conduct as and when they arise. The group meets on a weekly basis to discuss study progress.

The Trial Steering Committee provides overall supervision for the trial on behalf of the trial sponsor and to ensure that the study/trial is conducted according to the guidelines for Good Clinical Practice (GCP) and all relevant regulations and local policies.

A Data Safety Monitoring Board has also been established to maintain oversight of patient safety and data integrity within the trial.

### Composition of the data monitoring committee, its role and reporting structure {21a}

An independent Data Safety Monitoring Board (DSMB) has been established to safeguard the interests of trial participants, to assess the safety of the interventions during the trial and to assist and advise the principal investigator (PI) so as to protect the validity and credibility of the trial.

The DSMB will meet remotely (1) upon the opening of the trial, (2) at the end of each plague season and (3) at the end of the trial.

DSMB members:
[name], Chief of the Bacterial Diseases Branch (BDB), Division of Vector-Borne Diseases (DVBD), National Center for Emerging and Zoonotic Infectious Diseases (NCEZID), Centres for Disease Control and PreventionProfessor [name], Director Liverpool School of Tropical Medicine and Professor of Tropical Medicine, Liverpool School of Tropical Medicine, Pembroke Place Liverpool, L3 5QA, UKProfessor [name], Head of Biostatistics Unit/Deputy Head of School, Centre for Epidemiology and Biostatistics, Melbourne School of Population and Global Health, The University of Melbourne, Victoria 3010, Australia

### Adverse event reporting and harms {22}

Streptomycin and ciprofloxacin are approved drugs with well-established safety profiles. Serious adverse events/serious adverse reactions (SAEs/SARs) and suspected unexpected serious adverse reactions (SUSARs) will be reported in accordance with the international guidelines and applicable national legislation.

All adverse events (AEs) observed or reported by the patient should be recorded on the AE form within the CRF.

In the event of an adverse event or reaction, the investigator is responsible for providing an appropriate medical response, providing a causality assessment and monitoring the progress of the AE until it has resolved. In the event that an adverse event is deemed serious, according to the international definition (ICH), it should be notified immediately to IPM via the SAE report form within 48 h of the site becoming aware of the event. Newly arising SAEs must be reported from the point of consent until D21. All SAEs must be followed up by the site until resolution (including when resolution occurs after D21).

The following events, which are either classified as treatment evaluation criteria or inclusion criteria, are exempt from reporting as an SAE:
Respiratory symptoms (cough, tachypnea, haemotysis)Intestinal symptoms (diarrhoea, vomiting)FeverBuboPain at bubo’s site

In addition, the following circumstances should not be notified to the sponsor:
Routine examinationMedical/surgical/hospital procedure planned before inclusionA condition present before inclusion or discovered at inclusion (e.g. malaria discovered at inclusion and requiring hospitalization)

All SAEs/SARs reported to IPM will be notified to the sponsor within one business day and will be reviewed and evaluated by two clinical reviewers. If the reviewers have concerns about the SAEs submitted, an emergency meeting of the DSMB and the TOC will be convened to discuss the management of the SAE and the potential impact on the trial.

All SUSARs will be reported to the Centre National de Pharmacovigilance in Madagascar within 7 days for fatal or life-threatening reports and within 15 days for other serious, unexpected SARs for all initial reports.

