## Introduction

### Background and rationale {6a}

#### Plague

Plague is caused by the Gram-negative bacteria *Yersinia pestis*. There are three main clinical forms in which plague can manifest, sometimes with overlapping clinical syndromes: bubonic plague, septicaemic plague (primary or secondary) and pneumonic plague (primary or secondary) [1]. Bubonic plague is the most common clinical form and is characterized by the rapid onset of fever and tender and painful lymphadenopathy. It accounts for over 90% of plague cases [1]. Septicaemic plague is characterized by non-specific symptoms, as for septicaemia in general [1]. Pneumonic plague presents with rapid onset of fever and respiratory symptoms, with haemoptysis being a cardinal feature [1].

Plague is primarily present in Africa, although the USA and countries in Asia and South America are also affected. The incidence of plague continues to decrease (from 2683 cases notified to the WHO in 2008 to 243 in 2018) and geographical spread to shrink (98% of reported cases currently from just Madagascar and the Democratic Republic of Congo (DRC)) [2]. However, the reservoir and conditions for transmission are still present in many areas of the world, and there is a risk of outbreaks when plague hits densely populated areas, as in the 2017 large urban outbreak of predominantly pneumonic plague in Madagascar, with over 2400 suspected cases [3].

In the pre-antibiotic era, the case fatality rate (CFR) of plague was > 70% [4]. Antibiotics have significantly reduced mortality: for the cases notified to WHO during 2010–2018 CFR averaged 17% [2]. During the 2017–2018 plague outbreak in Madagascar, the CFR of confirmed pneumonic plague was 25% and bubonic plague 24% [3].

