##### Pneumonic plague

Patients of any ageRecent onset (< 7 days) of fever (uncorrected axillary temperature ≥ 37.5 °C) or history of feverCoughTachypnoea (respiratory rate > 24 in adults and age-specific in children)Epidemiological link with a confirmed or probable case of primary or secondary pneumonic plague within 7 days of onset of symptoms

A small proportion of patients with bubonic plague will also develop pneumonic plague. These patients will be randomized to receive pneumonic plague therapy. For a patient to be considered to have mixed bubonic and pneumonic plague, they must have developed cough and dyspnoea after the onset of the bubo.

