#### Route of administration

Streptomycin is administered intramuscularly to all patients in the control group. Ciprofloxacin is administered orally, except for patients with the following manifestations:
VomitingUnable to swallowUnconsciousSystolic blood pressure < 90 mmHgAny other conditions or situations for which the physician decides that intravenous treatment is indicated

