##### Pneumonic plague

Proportion of patients with a therapeutic response at D11. Therapeutic response is defined as follows:
◦ Alive◦ Resolution of fever (uncorrected axillary temperature < 37.5 °C)◦ Resolution of tachypnoea (RR < 24 in adults, but age-specific in children)Proportion of patients without fever (uncorrected axillary temperature < 37.5 °C) at D4Proportion of patients with tachnypnoea resolution (RR < 24 in adults, but age-specific in children) at D4Proportion of patients experiencing a serious adverse event on or before D4Proportion of patients experiencing a serious adverse event on or before D11Proportion of patients experiencing a serious adverse event on or before D21Proportion of patients who fully adhere to the study treatment schedule

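### The list of events exempt from SAE reporting contradicts its own rationale for five of eight symptoms in bubonic patients, so serious episodes of these can be missed by the SAE endpoints and expedited safety review

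*Protocol article*

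**What the plan says.** The section Adverse event reporting and harms {22} of the protocol article commits to the ICH definition of seriousness and to international reporting guidelines. It then states that certain events, "which are either classified as treatment evaluation criteria or inclusion criteria, are exempt from reporting as an SAE". Eight events follow: cough, tachypnoea, haemoptysis, diarrhoea, vomiting, fever, bubo and pain at the bubo. The list is the same for both clinical forms. It makes no exception for an episode that is life-threatening or judged to be drug-related.

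The same section describes what follows from a submitted SAE: notice to the sponsor within one business day, evaluation by two clinical reviewers and, if they are concerned, an emergency meeting of the DSMB and the Trial Operations Committee. It also says: "All adverse events (AEs) observed or reported by the patient should be recorded on the AE form within the CRF".

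Under Secondary endpoints, the proportion of patients with an SAE on or before D4, D11 and D21 is listed for bubonic and for pneumonic plague.

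**The concern.** Leaving disease events out of SAE reporting is sound when those events are already captured as entry conditions or outcomes, and that is the reason the article gives. The reason fails for several items on the list. Where it fails, a serious episode is exempt although nothing else in the endpoint set counts it.

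Two things are at stake. The SAE proportions are the only safety endpoints listed, and they would be incomplete for gastrointestinal and respiratory events. The expedited review described in the article also starts from submitted SAEs, so an exempt event does not start it. Respiratory events in bubonic patients matter here because the article expects that "A small proportion of patients with bubonic plague will also develop pneumonic plague", recognised by cough and dyspnoea after the bubo appears.

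**Working it through.** The article gives no figure to reproduce. The check sets each exempt event against the inclusion criteria (Eligibility criteria {10}) and the endpoints (Outcomes {12}).

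| Exempt event | Criterion or endpoint in bubonic plague | Criterion or endpoint in pneumonic plague |
|---|---|---|
| Fever | yes (inclusion, primary endpoint) | yes (inclusion, response) |
| Bubo | yes (inclusion, primary endpoint) | no |
| Pain at bubo | yes (tenderness at inclusion, pain score endpoints) | no |
| Cough | no | yes (inclusion) |
| Tachypnoea | no | yes (inclusion, response) |
| Haemoptysis | no | no |
| Diarrhoea | no | no |
| Vomiting | no | no |

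Counts:
- Bubonic: 3 of 8 fit the stated rationale and 5 do not.
- Pneumonic: 3 of 8 fit.
- Neither form: 3 of 8 (haemoptysis, diarrhoea, vomiting).

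Where the three unsupported events appear elsewhere:
- Haemoptysis appears only in the background description of pneumonic plague, "with haemoptysis being a cardinal feature". The pneumonic response definition has a respiratory item, "Resolution of tachypnoea (RR < 24 in adults, but age-specific in children", but does not mention haemoptysis.
- Vomiting appears only under Route of administration, in the list introduced by "Ciprofloxacin is administered orally, except for patients with the following manifestations". That is neither an entry condition nor an outcome.
- Diarrhoea appears nowhere else.

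What one missed patient does to an SAE proportion depends on the denominator, which the endpoint does not fix:
- Infected population at the planned size: 1/95 = 1.05 percentage points.
- All randomised bubonic suspects, about 600 in total: 600/2 = 300 per arm, and 1/300 = 0.33 percentage points.

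Exposure to ciprofloxacin by arm, from the dosing schedules:
- Bubonic: 10 days × 2 = 20 doses in the ciprofloxacin arm and 7 × 2 = 14 in control. If gastrointestinal events were proportional to ciprofloxacin doses, which is an assumption, the ciprofloxacin arm would have 20/(20 + 14) = 59% of them.
- Pneumonic: 10 × 2 = 20 doses in both arms, so there is no difference.

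**The case against.** Five points can be made for the article.

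1. The events are not lost. Every adverse event goes on the CRF form with a causality assessment, and symptoms and vital signs are recorded on D1 to D4, D11 and D21. This stands. The gap is in SAE reporting and what depends on it, not in the database. No listed endpoint uses the adverse event form, however.

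2. A reader might infer that progression to pneumonic plague is hidden. The documents do not support that. The list names symptoms; pneumonic plague, respiratory failure and death are not on it and remain reportable. Death is in the primary endpoint, and progression can count as failure through alternative treatment or continued antibiotics. What remains is narrower: a serious respiratory symptom in a bubonic patient, recorded as a symptom, is exempt.

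3. A reader might infer that the DSMB's routine data miss these events. The article does not say what the DSMB sees at its end-of-season meetings. Only the emergency trigger is shown to depend on submitted SAEs.

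4. A reader might infer from 20 against 14 doses that under-counting falls mainly in the ciprofloxacin arm. It does not follow. Even strict proportionality gives 59%, no event rate is given, and pneumonic patients have equal ciprofloxacin exposure.

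5. Cough and tachypnoea are inclusion criteria of the trial as a whole, so the rationale is literally true for them. That is a possible reading, but in a bubonic patient neither is an entry condition nor an outcome, so the reason for exempting them does not apply. The contradiction over haemoptysis, diarrhoea and vomiting holds on any reading.

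One further caution stands. The endpoint speaks of patients experiencing an SAE and the exemption of reporting one. That exempt events drop out of the endpoint is the natural reading, but the article does not say so.

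**Conclusion.** The point holds. The exemption list contradicts its stated reason for haemoptysis, diarrhoea and vomiting in both forms, and for cough and tachypnoea in bubonic patients. A serious episode of one of these need not be submitted as an SAE. It can therefore be missed by the SAE proportions at D4, D11 and D21, the two-reviewer evaluation and the emergency trigger.

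The effect on the SAE proportions cannot be sized, because the article gives no event rates. It rests on the assumption that those proportions are built from submitted SAE reports. No direction of bias between the arms is established.

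This should be fixed but is not critical. The SAE endpoints are secondary and summarised descriptively, and the primary non-inferiority conclusion is unaffected.

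**What to change.** Reconcile the list with the inclusion criteria and endpoints:

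- Remove diarrhoea, vomiting and haemoptysis.
- Limit the remaining exemptions to events that are criteria for the patient's clinical form at enrolment: fever, bubo and bubo pain for bubonic plague; fever, cough and tachypnoea for pneumonic plague.
- State which list applies to patients with mixed disease.
- State that any other such event meeting the ICH seriousness definition is submitted as an SAE and counted in the D4, D11 and D21 proportions.

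Serious tachypnoea in a pneumonic patient would stay exempt, which is consistent with the rationale because tachypnoea is assessed as an outcome in that form at D4 and D11.

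The cost is a short amendment, coverage at the retraining already planned for the start of each season, and a few more SAE forms. It changes a reporting rule and no treatment.

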### Frequency and plans for auditing trial conduct {23}

None.

### Plans for communicating important protocol amendments to relevant parties (e.g. trial participants, ethical committees) {25}

All protocol amendments will be discussed by the TOC which includes members from each of the study partners ahead of submission to the respective ethics committees. It is the responsibility of each institution to obtain their own ethical approvals. Only once all ethical approvals have been obtained will the amendment be implemented. It will be the responsibility of IPM to disseminate the changes to the protocol to participating sites.

### Dissemination plans {31a}

The principal publication of the study will be in the name of the investigators with full credit assigned to all collaborating investigators, research coordinators and institutions. Oral or written communications will acknowledge all trial stakeholders, either in the list of authors or in the acknowledgements, depending on their respective contributions to the trial and the presentations made. A drafting committee will be formed at the time of data analysis. The order of authors at publication will be equally contributed, by the importance of contribution or in alphabetical order. Results from the trial will be published in open-access journals, and the data will be available for sharing.

## Discussion

Conducting clinical trials of plague is operationally challenging, mostly because cases occur in rural places with difficult access to health facilities, especially because cases occur mostly during the rainy season, and are scattered over a vast territory. Communication and network coverage may be erratic, and security issues may also occur. This requires adequately staffed, well-trained study teams to be deployed over a number of peripheral health facilities, with logistical challenges and inherent high costs. This, plus the fact that drugs are registered for plague (based on the ‘animal rule’) and that national and international guidelines exist (based on empirical regimens), along with the general lack of funding options for plague, has essentially discouraged the conduct of treatment trials.

## Trial status

Protocol version number: 2.9

Protocol date: 27 September 2019

Recruitment start date: planned February 2020

Planned recruitment end date: March 2023

## Abbreviations

AE: Adverse event
C: Celsius
caf-1 gene: Chromatin assembly factor-1
CI: Confidence interval
CIOMS: Council of International Organizations of Medical Sciences
CLSI: Clinical & Laboratory Standards Institute
CPL: Clinical plague laboratory
CRF: Case report form
CSB: Centre de Santé de Base
D: Day
DFID: Department for International Development
DSMB: Data and Safety Monitoring Board
ELISA: Enzyme-linked immunosorbent assay
F1: Fraction 1 antigen
FDA: Food and Administration
GCP: Good Clinical Practice
GDPR: General Data Protection Regulation
IgG: Immunoglobulin G
IgM: Immunoglobulin M
Inv1100 gene: Chromosomal invasin gene
IPM: Institute Pasteur de Madagascar
ITT: Intention to treat
ITTI: Intention to treat infected
M3: Month 3
PI: Principal investigator
PP: Per-protocol
PPI: Per protocol infected
qPCR: Quantitative polymerase chain reaction
RCT: Randomized clinical trial
RDT: Rapid diagnostic test
RR: Respiratory rate
SAE: Serious adverse event
SAP: Statistical analysis plan
TOC: Trial Operations Committee
WHO: World Health Organization
WT: Wellcome Trust
